#### Data management

All data will be entered electronically in REDCap, a secure software data management platform [27]. To promote data quality, all variable coding has been consistently planned with required fields to reduce missing data, field notes explaining how to register a variable and validation for numerical variables. An independent data manager has double-checked all instruments in REDCap. Furthermore, only the project assistant and the independent project manager can access the database’s design and development. The others collecting data will only have the possibility to register in the database. It secures data quality and reduces bias.

#### Statistical analyses

Descriptive statistics will be applied to check for exchangeability between the two groups according to the variables measured at baseline and to assess the reproducibility of our sample with previous study within this field. Non-categorical data will be presented as mean and standard deviation (SD) and analyzed using a *t*-test or median and interquartile ranges (IQR) analyzed with Wilcoxon rank sum test, depending on whether the given variable follows a normal distribution. Depending on Cochran’s rule, categorical data will be presented as numbers (*n*) or proportions (%) and analyzed with either a Fisher or chi-square test, depending on Cochran’s rule.

Besides the descriptive statistics, margin plots for the primary and secondary outcomes will be constructed to assess whether the treatment effect changes over time.

The final manuscript will report 95% confidence intervals and two-sided *p* values. A *p* value below 0.05 will be considered statistically significant and multiple testing will be handled by using Hochberg’s sequential procedure. All data will be analyzed in STATA/BE version 18.

##### Primary analysis

The primary analysis will be a beta-binomial mixed effect model, thus adopting a subject-specific approach. We will incorporate an interaction between group and time if necessary, to accommodate varying treatment effects over the time period. Therefore, we will present the estimates for each time point (baseline, at 3, 6, and 12 months) and construct a margin plot based on the model. We will conduct a likelihood ratio test to test whether our intervention affects the primary outcome across all time points. If the test is statistically significant, we will conduct a *z*-test at each time point to assess when there is a statistically significant treatment effect. Here, we will utilize G-computation to acquire interpretable effect sizes on both the mean ratio and mean difference scales for sensitivity purposes. In the G-computation, the Q-model will be a mixed-effect model, and the prediction will be based solely on the fixed effect. To avoid inflating the type I error rate in the bootstrapped *z*-test, we will adjust the *z*-test for multiple tests.

If the beta-binomial regression has difficulties converging, we will adopt a mixed-effect model with bootstrapped confidence intervals. Here, we will choose restricted maximum likelihood and the Kenward method for calculating the degrees of freedom and test whether a random slope shall be incorporated by way of an *F*-test.

The primary analysis will follow the intention-to-treat principle; hence, missing data will be managed. As the beta-binomial mixed effect model regression uses maximum likelihood estimation, we can assume that the beta regression will yield unbiased results if the data is missing at random or completely at random. However, under the assumption of missing not at random, the estimates from the beta regression will be biased; therefore, we will conduct joined modeling to assess the influence of missing data if the data was missing not at random. In the joint model, we will use Cox regression to estimate the censoring weights.

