## Outcomes

### Primary outcome

#### The Oxford shoulder score (OSS) questionnaire

The primary endpoint is the patient-reported shoulder function assessed by the Oxford shoulder score 12 months after surgery reported in mean [11]. The OSS comprises 12 items: four assessing the degree of pain and eight evaluating function. Each item is rated on a 5-point Likert scale, where 0 indicates the worst outcome, and 4 indicates the best. The scores from these 12 items are summed to produce a total score ranging from 0 to 48 [11].

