### Secondary outcomes

#### The Oxford shoulder score questionnaire

Improvements in the Oxford shoulder score as above [11] measured 3 and 6 months post-surgery compared to baseline.

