##### Secondary analysis

The analysis of EQ-5D will follow the same principle as the primary outcome. Generalized linear mixed-effect models will be chosen for all secondary outcomes and utilize the same parameterization as the primary outcome analysis. For EQ-5D-VAS, pain, supraspinatus healing, and fatty degeneration, we will use a mixed-effect beta-binomial regression, and if convergence fails, we will perform a mixed-effect linear regression with bootstrapped 95% confidence intervals (CI). Concerning the outcomes measuring pain-free movement above the shoulder (yes/no) and supraspinatus atrophy (yes/no), we will use a mixed-effect logistic model. For outcomes relating to MRI and STU assessment, we will utilize a mixed-effect model. If the model fit for the mixed-effect model is deemed unacceptable. First, a log transformation of the outcome will be utilized, and if the fit is still unsatisfactory, we will use a mixed-effect gamma regression.

If any regression analyses produce problematic effect sizes, we will use G-computation, assuming the Q-model is the appropriate generalized linear model analysis for the given outcome. Additionally, we will account for the longitudinal aspect using multiplicative interaction and baseline restriction.

Interim analysis only concerning adverse events will be performed for every 5 patients included, and early trial cessation is possible if there are any safety concerns. This analysis will be presented descriptively.

Sensitivity analyses will be conducted to compare the standard care and intervention groups across each domain of the OSS and EQ-5D. These analyses will track changes in each domain’s response trajectory from baseline to 3, 6, and 12 months post-surgery. The results will be descriptively analyzed and graphically presented using radar plots.

To enhance retention and minimize loss to follow-up, we will have an automated electronic system for scheduling and reminders for upcoming visits at the outpatient clinic. Additionally, we will offer flexible appointment times to better accommodate participants’ schedules. We will continuously monitor retention rates and proactively reach out to patients in the event of missed appointments.

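### The primary analysis of the Oxford shoulder score does not single out the 12-month difference that the protocol names as its one primary endpoint

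*Protocol article*

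**What the plan says.** The Primary outcome section is clear: "The primary endpoint is the patient-reported shoulder function assessed by the Oxford shoulder score 12 months after surgery reported in mean". Under Secondary outcomes, improvement in the same score is "measured 3 and 6 months post-surgery compared to baseline", so the 3- and 6-month scores are secondary.

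The Primary analysis section then describes a beta-binomial mixed model over all visits, with these steps:

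- **Interaction:** "We will incorporate an interaction between group and time if necessary, to accommodate varying treatment effects over the time period". No criterion is given.
- **Gate:** "We will conduct a likelihood ratio test to test whether our intervention affects the primary outcome across all time points".
- **Visit tests:** "If the test is statistically significant, we will conduct a *z*-test at each time point to assess when there is a statistically significant treatment effect".
- **Multiplicity:** "we will adjust the *z*-test for multiple tests", with no method named at that place.

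The general rule under Statistical analyses is that "multiple testing will be handled by using Hochberg’s sequential procedure". The Sample size section bases its p value on the 12-month difference, but with a Bonferroni correction. The Secondary analysis section adds that "we will account for the longitudinal aspect using multiplicative interaction and baseline restriction".

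**The concern.** A single primary endpoint at one visit calls for one contrast, fixed in advance, whose result decides the trial. The steps above answer a different question: whether there is an effect at any visit and, if so, when. Three consequences follow.

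1. If the interaction is left out, the model has one group effect common to all visits, and that is not the 12-month difference.
2. The 12-month result depends on a test that also carries the secondary visits, and it then shares alpha with them.
3. The gate can be passed by early effects alone. The article does not say how such a trial would be read.

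**Working it through.** **Inputs.** From Table 1: control means 19, 28, 30, 33 (SD 4.12 throughout); intervention means 19, 40, 36, 41 (SD 4.12, 3, 3.6, 3.6). The visit differences are therefore 0, 12, 6 and 8. From Sample size and Statistical analyses: 15 per arm, stated power 94%, alpha 0.05, two-sided p values. The correlation between visits is not given, so it is assumed below.

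**1. The plan's own power figure.** Take a linear regression on 2 × 4 × 15 = 120 observations with group-by-time, testing the 12-month interaction coefficient (change from baseline).

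- Pooled variance: (5 × 4.12² + 3² + 2 × 3.6²)/8 = (84.87 + 9 + 25.92)/8 = 14.97, so the SD is 3.87.
- SE = 3.87 × √(4/15) = 2.00; non-centrality 8/2.00 = 4.00; 120 − 8 = 112 df.
- With alpha 0.05/3 (critical t 2.43), power is 94.0%, as stated. Division by 2 gives 95.7% and by 4 gives 92.6%.
- A plain two-sample comparison at 12 months has SE 3.87 × √(2/15) = 1.41 and power above 99.8%, with or without the division by 3. It does not reproduce 94%.

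The sample size thus appears to rest on a group-by-time contrast, the term that the Primary analysis makes conditional. This is inferred, because the Do-file is not shown.

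**2. What the model estimates without the interaction.** In a balanced linear random-intercept model, used here as a mean-scale approximation to the beta-binomial model, the common effect is the average of the visit differences:

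- with baseline as an outcome row: (0 + 12 + 6 + 8)/4 = 6.5
- over post-surgery visits only: (12 + 6 + 8)/3 = 8.67

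Neither is the 12-month value of 8.

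**3. How likely the interaction is to be dropped under Table 1.** Suppose the need for it is judged by an F test on 3 and 84 df, with λ = (15/2) × Σ(d − mean d)² / [SD² × (1 − ρ)]. Here Σ(d − 6.5)² = 42.25 + 30.25 + 0.25 + 2.25 = 75, so the numerator is 562.5.

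| SD | ρ | λ | Power of interaction test |
|---|---|---|---|
| 4 | 0.3 to 0.5 | 50 to 70 | about 100% |
| 8 | 0.3 | 12.6 | 84% |
| 8 | 0.5 | 17.6 | 95% |

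At SDs near those of Table 1 the term would almost never be dropped.

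**4. What the gate and adjustment do (simulation, normal data, 15 per arm, tests at 3, 6 and 12 months).**

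| Effects at 0/3/6/12 months | SD, correlation | Gate plus adjusted 12-month test | Single 12-month test at 0.05 |
|---|---|---|---|
| 0/12/6/8 (Table 1) | 3.87, 0 to 0.6 | about 99.9% | over 99.9% |
| 0/0/0/4 (assumed) | 3.87, 0 to 0.6 | 61 to 66% | 81% |
| 0/2/4/8 (assumed) | 8, 0.5 | about 70% (65 to 74% by covariance handling) | about 85% |
| no effect at any visit | 3.87, 0 to 0.6 | about 1.2% | 5% |

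In the 0/2/4/8 row both approaches use baseline in the same way, so the gap is due to the gate and the adjustment alone.

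For assumed effects of 0/12/6/0 at SD 3.87, the gate passes in about 100% of trials. In about 95% some visit is declared significant under Hochberg but month 12 is not.

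**The case against.** The strongest reply is that the endpoint hierarchy is already fixed. The abstract, the objectives and the Primary outcome section all name 12 months, the power calculation uses the 12-month difference, and a 12-month z-test is among those planned. That stands: it would be wrong to say that the plan has no 12-month test, and no sentence allows a positive claim on 3 months alone. What is missing is a sentence making the 12-month test decisive, and the stated gate works against it.

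A reader might infer that the 12-month effect will be badly diluted. The documents do not support that. The plan promises estimates for each time point, which makes sense mainly with the interaction in the model, and step 3 shows that the Table 1 pattern would almost always keep it. The baseline restriction named under Secondary analysis would also remove the pull from the baseline row. But that sentence stands under Secondary analysis and does not lift the condition in the Primary analysis.

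A reader might also infer a planned z-test at baseline. Baseline appears in the list of time points for which estimates are presented, not in the sentence on testing, so this is a possible reading only. Nor are there three conflicting multiplicity rules. The adjustment left unnamed in the Primary analysis is covered by the general Hochberg rule, and planning with Bonferroni is conservative, because Hochberg rejects whenever Bonferroni does.

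Finally, gating and then adjusting is a valid, conservative procedure, and a criterion for including the interaction could be left to an analysis plan. Both are fair. The order of testing, however, is stated here and does not fit the stated endpoint; an analysis plan would have to overrule it, not merely complete it.

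**Conclusion.** The point holds as a mismatch between endpoint and primary test, and it should be fixed. The 12-month contrast is neither guaranteed its own term in the model nor named as the deciding test.

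Under the Table 1 effects and SDs the practical loss is close to nil, and false positives at 12 months are not inflated. The loss of roughly 15 to 20 points arises only with smaller or late effects or a larger SD. Those effect patterns, the SD of 8 and the visit correlations are assumptions and are not in the article. The 6.5 and 8.67 figures apply only if the interaction is dropped, and they use a linear approximation. What does not depend on these assumptions is the ambiguity: a trial with early effects and none at 12 months would pass the gate, and the plan does not say how to call it.

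**What to change.** In the Primary analysis section, state that:

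- the model always contains group-by-time, with baseline means constrained equal in the two arms (the baseline restriction already named under Secondary analysis);
- the sole primary test is the 12-month group difference at two-sided 0.05, with no gate and no multiplicity adjustment;
- no test is made at baseline;
- OSS at 3 and 6 months is tested in the secondary family under Hochberg, and the all-visit likelihood ratio test is descriptive.

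In the Sample size section, align the Bonferroni wording with this and restate the power. Under Table 1 it becomes 97.8% for the change-from-baseline contrast that reproduces 94%, and over 99.9% for the direct 12-month comparison, so 30 patients remain enough on those assumptions.

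The cost is wording only. The omnibus test loses its confirmatory role.

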##### Secondary analysis

The analysis of EQ-5D will follow the same principle as the primary outcome. Generalized linear mixed-effect models will be chosen for all secondary outcomes and utilize the same parameterization as the primary outcome analysis. For EQ-5D-VAS, pain, supraspinatus healing, and fatty degeneration, we will use a mixed-effect beta-binomial regression, and if convergence fails, we will perform a mixed-effect linear regression with bootstrapped 95% confidence intervals (CI). Concerning the outcomes measuring pain-free movement above the shoulder (yes/no) and supraspinatus atrophy (yes/no), we will use a mixed-effect logistic model. For outcomes relating to MRI and STU assessment, we will utilize a mixed-effect model. If the model fit for the mixed-effect model is deemed unacceptable. First, a log transformation of the outcome will be utilized, and if the fit is still unsatisfactory, we will use a mixed-effect gamma regression.

If any regression analyses produce problematic effect sizes, we will use G-computation, assuming the Q-model is the appropriate generalized linear model analysis for the given outcome. Additionally, we will account for the longitudinal aspect using multiplicative interaction and baseline restriction.

Interim analysis only concerning adverse events will be performed for every 5 patients included, and early trial cessation is possible if there are any safety concerns. This analysis will be presented descriptively.

Sensitivity analyses will be conducted to compare the standard care and intervention groups across each domain of the OSS and EQ-5D. These analyses will track changes in each domain’s response trajectory from baseline to 3, 6, and 12 months post-surgery. The results will be descriptively analyzed and graphically presented using radar plots.

To enhance retention and minimize loss to follow-up, we will have an automated electronic system for scheduling and reminders for upcoming visits at the outpatient clinic. Additionally, we will offer flexible appointment times to better accommodate participants’ schedules. We will continuously monitor retention rates and proactively reach out to patients in the event of missed appointments.

### Monitoring

The project assistant responsible for managing and developing the study database will monitor data collection to ensure minimal missing data. The project assistant has no role in screening, the surgery, or allocation performance but will assist in clinical assessment if needed, such as collecting demographic information from patients and performing STU. The project assistant will monitor the daily inclusion of participants and discuss with the project group.

After the primary data analysis, the results will be discussed and evaluated by the project group and all involved, including the hospital department.

### Adverse events, complications, and risks

The liposuction procedure is safe with a very low risk of complications (less than 1%), such as bleeding, infections, and scarring [40]. In rare cases, there may be bleeding, and a reoperation or puncture of the skin may be necessary. An infection is rarely seen and can be treated with antibiotics, and in exceptional cases, additional surgery may be required. Sensory disturbances might be seen at the donor site. These fade away generally within 3–6 months, but in some individuals, it may be permanent (less than 1%).

Harvest of 0.1–0.2 g muscle biopsies from the supraspinatus muscle is performed under direct vision from the arthroscope and has been performed without complications in 42 patients in a former protocol (Projekt-ID: S-20160037).

MRI and ultrasonography have no reported risks or adverse effects.

The responsible surgeon or physician will report adverse events in the study database at the time they occur. All adverse events occurring during surgery, post-surgery, and up to the final follow-up at 1 year will be documented. Adverse events that occur after a subject has been discontinued from the study will not be reported unless the investigators suspect they are related to the stem cell treatment procedures. We will record adverse events and any negative effects of the intervention using a structured template that allows for additional comments in free text within the electronic database (REDCap). For each event, we will document the date, type of adverse event, or negative effect (e.g., infection, skin and subcutaneous tissue disorders, increased pain, reduced strength, reduced mobility, reduced sensitivity, or other issues). Any identified harms will be detailed in future publications.

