#### Blinding

Patients, project assistants, physicians, and outcome adjudicators are not blinded to randomization due to practical constraints. The radiologist and the statistician performing the analysis will be blinded.

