#### Reasons for early study termination

Continued analysis for safety will be performed regarding the presence of major adverse events, and an interim analysis will be formed after every five patients are included. Major adverse events are defined as postoperative complications requiring active treatment (the Clavien-Dindo classification grade III and above). In case of exclusion, patients are offered standard treatment according to hospital standards. The study will be terminated early if this analysis reveals the presence of major adverse events in 50% or more in one arm of the study. The Danish Patient Compensation covers patients enrolled in this study.

Only the project assistant who developed the study database and monitors the data will have access to the interim analysis. This assistant will extract a predefined report containing only reported adverse events, ensuring that all other data remains confidential. If adverse events are identified, they will be presented to the study group, including the principal investigator, and an audit will be performed before deciding whether to terminate the trial. There will not be a possibility of modifying the intervention, but patients will receive standard treatment.

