## Ethics and dissemination

### Research ethics approval

The study protocol, version 8, was approved by the Regional Committees on Health Research Ethics for Southern Denmark on June 27, 2024 (S-20230073), registered by the Danish Data Protection Agency (Journal nr.: 24/26916) and by the ClinicalTrials.gov (NCT06505135).

The study will be conducted according to the study protocol, which conforms to the current health legislations and good clinical practice (ICH-GCP), and written informed consent will be obtained from the participants before participation in the study (Additional file 3). Participation is voluntary, and patients may withdraw their consent at any time without consequences for further treatment. The data collected from discontinued patients will be deleted and will not be part of the analysis.

To protect patient confidentiality, the personal data collection will be registered in the REDCap electronic database [27], data extraction for data analysis will be pseudonymized, and the results data will be presented anonymously. The patient will be informed both verbally and in writing that the tissue sample will be stored in a research biobank at the Department of Pathology in Odense, along with details about any future analyses. Participants will have no financial gain by participating in the study. The advantage for the patients may be improved rehabilitation and reduced risk of fibrosis. Stem cell therapy has, however, been shown to be safe. Intra-articular injection of the lipoaspirate is formerly approved to be used at Hvidovre Hospital (Danish National Committee on Health Research Ethics (H-18013145) and the Danish Data Protection Agency (VD-2018–141)). This study can potentially establish the fundaments of a safe treatment for an otherwise difficult surgical condition.

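### After discontinuation, adverse events are reported only if suspected to stem from procedures that the intervention arm alone receives, so counts by arm do not rest on the same basis

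*Protocol article*

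**What the plan says.** Under Adverse events, complications, and risks, the Protocol article sets a general rule: "All adverse events occurring during surgery, post-surgery, and up to the final follow-up at 1 year will be documented". It then makes an exception for discontinued subjects, whose later events "will not be reported unless the investigators suspect they are related to the stem cell treatment procedures". On who reports, the same section says: "The responsible surgeon or physician will report adverse events in the study database at the time they occur".

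The Blinding section states: "Patients, project assistants, physicians, and outcome adjudicators are not blinded to randomization due to practical constraints". Only the radiologist and the analysing statistician are blinded. The Stem cell treatment section gives the additional procedures to the intervention group, on top of the standard repair that both groups have.

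Adverse events are used in two ways. Harms are to be detailed in publications, and an interim safety look follows every five patients included. For that look, Reasons for early study termination says: "The study will be terminated early if this analysis reveals the presence of major adverse events in 50% or more in one arm". The interim report holds reported adverse events only.

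Research ethics approval adds, directly after the right to withdraw consent: "The data collected from discontinued patients will be deleted and will not be part of the analysis". It makes no exception for safety data.

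**The concern.** Suspected relation to a procedure is normally an attribute recorded for each event. Here, after discontinuation, it decides whether the event is recorded at all, and the procedure in question exists in one arm only. Two patients with the same late event, one per arm, are handled differently: the control's event is left out, and the intervention patient's event is reported if an unblinded investigator suspects the stem cell procedures. Complications of the tendon repair, which both arms undergo, are left out in both.

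At stake is whether a table of adverse events by arm can be read at face value. The trial adds a new procedure to standard surgery in 15 patients per arm, so one patient is 1/15 = 6.7 percentage points of an arm. This is a data-collection rule, so an analysis plan cannot repair it afterwards.

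**Working it through.** The plan states no figure on this point, so there is none to reproduce. The check is of the wording first, and then of the possible size.

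**Who can meet the exception**

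| Event | Control arm | Intervention arm |
|---|---|---|
| Before discontinuation | Recorded | Recorded |
| After discontinuation, from the tendon repair | Not reported | Not reported, unless attributed to the stem cell procedures |
| After discontinuation, possibly from harvest or injection | Cannot arise | Reported if suspected |
| After discontinuation, any other cause | Not reported | Reported only if suspected |

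The first row is subject to the deletion rule in Research ethics approval. One narrow route for controls remains. The muscle biopsy is described under the Stem cell treatment heading, but its text does not limit it to that group, whereas the injection text does. If controls are biopsied, and if the biopsy counts as a stem cell treatment procedure, a control event related to it could qualify.

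**Possible size if true risk is equal**

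Inputs:
- n = 15 per arm (Sample size section).
- d = patients discontinued per arm, assumed 1 to 3; not in the documents.
- p = true risk of an event after discontinuation, assumed 0.2 to 0.5 and equal in both arms; not in the documents.
- s = probability that an investigator suspects the stem cell procedures, assumed 0.25 to 1; not in the documents.

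Expected reported events are d × p × s in the intervention arm and d × p × 0 = 0 in the control arm. As a share of the arm, the gap is 100 × d × p × s / 15.

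| d | p | s | True events per arm | Reported, intervention | Reported, control | Gap (points) |
|---|---|---|---|---|---|---|
| 1 | 0.2 | 0.25 | 0.2 | 0.05 | 0 | 0.3 |
| 2 | 0.5 | 0.5 | 1.0 | 0.5 | 0 | 3.3 |
| 3 | 0.2 | 1 | 0.6 | 0.6 | 0 | 4.0 |
| 3 | 0.5 | 1 | 1.5 | 1.5 | 0 | 10.0 |

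Under one rule for both arms, the expected gap at equal true risk is 0.

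**Direction**

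Let the true risks differ, pI in the intervention arm and pC in control. The true difference is d × (pI − pC) and the reported difference is d × pI × s. With d = 2, pI = 0.5 and pC = 0.2, the true difference is 2 × 0.3 = 0.6 events. At s = 0.25 the report shows 2 × 0.5 × 0.25 = 0.25, which understates it. At s = 1 it shows 2 × 0.5 × 1 = 1.0, which overstates it. The two agree only at s = 1 − 0.2/0.5 = 0.6. The rule can hide excess harm or create it, depending on an unblinded judgement.

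**Stopping rule**

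At full size, 50% of 15 is 7.5, so 8 patients with a major event in one arm are needed. A gap of at most 1.5 events is unlikely to decide that. At the first look, after five patients, an assumed 2:3 split (block sizes are not given) makes one event in the arm of two equal to 1/2 = 50%. One event counted or not could then matter, though few patients are likely to have discontinued so early.

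**The case against.** The strongest reply is that the flaw is narrow. *Discontinued from the study* most naturally means withdrawal of consent: surgery and injection are single events, so there is little treatment left to stop, and missed visits are handled separately by outreach and by the missing-data methods. If most discontinued patients have refused further contact, a better rule would recover few events. This stands as a limit on the size, but the documents do not define the term, and the exception itself presumes that some later events will be known.

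Four stronger readings are tempting, and the documents do not support them:

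- **That control-arm events in general go unreported.** They do not. The general rule covers both arms until discontinuation.
- **That a planned safety test is biased.** The article describes no formal between-arm test of adverse events. The interim look is descriptive and harms are to be described in publications. The harm is to the reading of descriptive counts.
- **That the stopping rule is undermined.** It is an absolute 50% threshold within one arm, not a contrast of arms, and an audit comes before any decision. The effect is likely small except at the first looks.
- **That the section contradicts itself.** The sentence on discontinued subjects is an explicit exception to the sentence before it.

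The loss of repair-related events is also broadly symmetric. It makes the harms record incomplete, but it is not what makes the arms differ. Nothing in the text shows that patients who discontinue are more likely to have had a problem.

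**Conclusion.** The concern holds for events after discontinuation. The condition for reporting can be met in the intervention arm, on an unblinded judgement, and essentially not in the control arm, apart from the possible biopsy route. Descriptive adverse-event counts by arm therefore do not rest on the same basis.

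The size is unknown, because the number of discontinuations is not given. The range of 0.3 to 10 percentage points rests entirely on the assumed values of d, p and s. The low end is 0.05 of an event and may be negligible in practice. The direction of the net distortion cannot be stated.

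The deletion sentence in Research ethics approval must be reconciled with this rule. If deletion covers all data of discontinued patients, their earlier events are lost in both arms. If the exception survives deletion, the only events left from discontinued patients would be those attributed to the stem cell procedures. The text does not say which applies. This is a moderate flaw that is cheap to correct, and it does not threaten the trial's primary result.

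**What to change.** Replace the sentence on discontinued subjects with one rule for both arms, for example: *Adverse events in both groups are recorded up to the 12-month follow-up, including after a patient has been discontinued from the study, unless the patient withdraws consent to further data collection.* Record suspected relation to each procedure (tendon repair, fat harvest, muscle biopsy, injection) as a separate field for every event, and never as a condition for entry. Tabulate events by randomised arm.

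Amend the deletion sentence in Research ethics approval to match, so that adverse events already recorded for discontinued patients are kept where consent allows.

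The cost is a relatedness field in REDCap and a few extra contacts or record checks. Because two sections change, and possibly the consent text too, the change should go to the ethics committee as the Protocol amendments section foresees.
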